**1. Project summary**

The objective of current study is to evaluate the effects of phantom exercises on phantom limb pain, mobility status, and quality of life in lower limb amputees treated with mirror therapy and routine physiotherapy. Twenty-four individuals with lower leg amputation participated in this trial and were randomly assigned to two equal groups. Limb Deficiency and Phantom Limb Questionnaire was used for screening of the participants. Other tools were Visual analogue scale (pain), Amputee mobility predictor (Ambulatory status) and 36-Item Short-Form Health Survey questionnaire (Health-related quality of life). The study was conducted in 12 months and data obtained was analysed through Statistical Package for Social Sciences (SPSS) 25.0 (*IBM, New York, USA*). The intervention lasted for 4 weeks. The control group underwent mirror therapy and conventional physical therapy while the experimental group performed phantom exercises additionally. Data was collected at baseline, after two and four weeks of intervention using. Mean age of the participants in experimental and control groups was 45.3±11.1 years and 40.5±12.5 years respectively. Both groups were comparable at baseline. After intervention, pain was significantly lower in the experimental group (p<0.05). Similarly, the experimental group demonstrated significantly better score in the “bodily pain” domain of SF-36 (p<0.05). Both groups improved in other domains of SF-36 and ambulatory potential with no significantly between-group differences after intervention. It was concluded that addition of phantom exercises resulted in significantly better pain management in lower limb amputees treated with mirror therapy and routine physiotherapy.

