As an alternative to MT, virtual reality training (VRT) can also be used to manage PLP, especially in patients with bilateral limb amputations. Despite the effectiveness of immersive virtual reality training, it uses are limited due to high cost. Because of high prevalence of PLP and its consequences on physical and mental health of amputees, there is a need to design easily administered, home-based and effective treatment protocol. The effects of phantom exercises, in conjunction with mirror therapy, for managing PLP in lower limb amputees are largely unknown. Therefore, the main objective of the current study was to evaluate the effects of phantom exercises on phantom limb pain, mobility status, and quality of life in lower limb amputees treated with mirror therapy and routine physiotherapy. It was hypothesized that addition of phantom exercises would result in significantly improved clinical outcome in all studied parameters.

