**4. Methodology**

*4.1 Patient information*: The mean (standard deviation) age of patients in the experimental and control group was 45.3(11.1) years and 40.5(12.5) years correspondingly. Vast majority of the patients underwent amputation within 2 years prior to this trial (experimental group =10; control group = 11). The number of male patients in experimental and control group was 8 and 9 respectively. Most patients reported right-handedness except for 1 patient in each group. The patients were recruited via non-probability convenience sampling. Thirty lower limb amputees were screened for eligibility through Limb Deficiency and Phantom Limb Questionnaire among other criteria.

*4.2 Eligibility Criteria:*

*4.2.a Inclusion Criteria:*

- Ages Eligible for Study: 18 Years to 50 Years (Adult)
- Accepts Healthy Volunteers: No
- Unilateral lower limb amputation
- Phantom limb pain score (40-100 on VAS)
- Either gender
- Stable prosthetic situation (i.e., satisfaction with the fitting of the prosthesis) or being a non-user.

*4.2.b Exclusion Criteria:*

- Amputees with psychological/neurological impairments.
- Amputees having neuropathic pain other than phantom limb pain.
- Patients having visual-spatial impairments.
- Taking pain relief medications will also be excluded.
- Patients having residual limb pain.
- Inability to give informed consent.
- Carcinoma
- Infectious stump
- Severe hearing loss
- Any condition that restricts the movement of opposite limb, pain or limited range of motion in the intact limb
- Infectious and systematic diseases

*4.3 Sample size:* Sample size is 6 in each group calculated by openEpi (24). We included 12 patients in each group.

*4.4 Setting:* Pakistan Society for the Rehabilitation of the Disabled (PSRD) and Hope foundation for rehabilitation sciences, Lahore, Pakistan.

*4.5 Rehabilitation protocols*: Both study groups received mirror therapy (15 minutes) and routine physical therapy (20 minutes) while the experimental group was given Phantom Motor Execution (PME), also known as phantom exercises, additionally (15 minutes).

*4.5.a Phantom Motor Execution:* Phantom exercises included imagining movement of the phantom limb and attempting to execute these movements. The patients were asked:

1. About position at which they were feeling their phantom limb.
2. To place their intact limb at same position as they felt their phantom limb.
3. To move their both limbs in opposite direction.

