4. To return back to their starting position. (24)

The movements included ankle inversion/eversion, flexion/extension, adduction with flexion of toes as clenching, abduction with extension of toes as unclenching. After patient feel relaxation, movements as knee flexion/ extension or hip flexion/ extension were repeated, until the PLP disappeared. (19) Phantom exercises were repeated until the PLP subsided completely with a maximum of 15 repetitions in one session.

*4.5.b Mirror therapy*: A standing flat mirror was used to perform 15 minutes of mirror therapy under physiotherapist’s supervision every day for 4 weeks. Sources of external stimulations (noise, television) were minimized, all accessories on the sound limb were removed, and patient’s comfort was ensured before the start of each session. Goals and benefits of mirror therapy were explained to the patients who were encouraged to ask questions. Pain level was measured on VAS prior to each session and rules of mirror therapy were instructed.

*4.5.c Routine physiotherapy*: The regimen comprised stretching of the tight musculature, static and dynamic muscle strengthening. Participants were also advised to keep a log of nature, frequency and duration of their physical activities. (20)

*4.6 Primary Outcome Measures:*

*4.6.a Visual analogue scale (VAS)* [ Time Frame: 4 weeks]

changes from the baseline, the visual analogue scale The VAS evaluates pain subjectively. It consists of a 100-mm line, with two endpoints representing "no pain" to "worst pain imaginable from left to right." Patients are instructed to mark on the line according to the level of pain and the same is measured

*4.6.b Amputee Mobility predictor* [ Time Frame: 4 weeks]

changes from the baseline, Amputee mobility predictor (AMP) is an amputee-specific tool for predicting ambulatory potential. This clinical test evaluates the predicted mobility of amputee with and without a prosthesis The AMP is a clinical test consisting of 20 tasks that are given a score of 0, 1, or 2 based on the amputee's performance. There is an item 21 where a score is given ranging from 0 to 5.

*4.6.c Limb Deficiency and Phantom Limb Questionnaire* [ Time Frame: day 1]

Patients will be evaluated using "Limb Deficiency and Phantom Limb Questionnaire (Questionnaire 2008, Version 2)" in order to assess their eligibility for including in this study.

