This questionnaire does not have any scoring, it only concludes the questions on Yes/No basis for presence or absence of phantom limb pain.

*4.7 Secondary Outcome Measures:*

*4.7.a Short form 36 (SF-36)* [ Time Frame: 4 weeks]

changes from the baseline, the 36-Item Short-Form Health Survey questionnaire (SF-36) is a very popular instrument for evaluating Health-Related Quality of life (HRQOL). It is a widely used valid and reliable tool for measuring the (HRQOL) and it can be employed in both the healthy and diseased population such as amputees for assessing the outcome of health care services and the effect of medical intervention.

The SF-36 measures eight scales: physical functioning (PF), role physical (RP), bodily pain (BP), general health (GH), vitality (VT), social functioning (SF), role emotional (RE), and mental health (MH). Component analyses showed that there are two distinct concepts measured by the SF-36: a physical dimension, represented by the Physical Component Summary (PCS), and a mental dimension, represented by the Mental Component Summary (MCS).

*4.8 Equipment:*

Therapy mirror: A standing mirror (130 cm × 46 cm) with wooden frame and base (62 cm × 65 cm)

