**7. Data management and statistical analysis**

Normality of the data was assessed through Shapiro–Wilk test. Multivariate analysis of variance was used to analyse training-induced changes in both groups. Between-group differences were computed with Mann-Whitney U test for VAS (pain) and second domain of SF-36. Independent samples t-test was used for AMP and remaining domains of SF-36. All statistical analyses were done with IBM SPSS 25.0 (*IBM, New York, USA*). Alpha level of significance was set at 0.05.

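### Two unranked testable primary outcomes and eight SF-36 domains are each tested at an unadjusted 0.05 with no success rule, and a third listed primary is an unscored eligibility screen

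*Combined protocol and SAP*

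**What the plan says.** Section 4.6 of the combined protocol and SAP puts three measures under primary outcomes, with no order among them: VAS pain and AMP, both as change from baseline with a 4-week time frame, and the Limb Deficiency and Phantom Limb Questionnaire on day 1. The questionnaire is given "in order to assess their eligibility for including in this study", and the text adds "This questionnaire does not have any scoring". Section 4.7 makes SF-36 secondary, with eight scales; the two component summaries (PCS and MCS) are described there but do not appear in the analysis.

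Sections 4.10 and 7 name a Mann-Whitney test for VAS and one SF-36 domain, and t-tests for AMP and the other domains. The only statement about error is "Alpha level of significance was set at 0.05". A MANOVA is mentioned for changes in both groups. Outcomes are collected at weeks 2 and 4 (sections 4.9 and 6), but the analysis text does not say which visit the between-group tests use.

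The hypothesis in section 2, repeated in section 9, is that "addition of phantom exercises would result in significantly improved clinical outcome in all studied parameters". The project summary in section 1 reports p<0.05 for pain and for SF-36 bodily pain, then states "Both groups improved in other domains of SF-36 and ambulatory potential with no significantly between-group differences after intervention". It concludes in favour of the added exercises for pain management.

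**The concern.** A primary outcome is what the trial is judged on. Here one of the three is measured before treatment, has no score and serves to admit patients, so it cannot carry a treatment comparison. The other two are unranked, and nothing says whether one win is enough, both are needed, or one takes precedence. This matters because the summary reports a split result: VAS differed and AMP did not.

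If success means whichever outcome reaches 0.05, the 5% level does not hold for that claim. The same applies to bodily pain, which is one of eight domain tests but is presented beside VAS as support. A reader given only p<0.05 cannot tell whether either pain finding would survive an adjustment for the number of tests.

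**Working it through.** **Inputs from the documents**
- Per-test alpha 0.05 (sections 4.10 and 7). Sidedness is not stated; two-sided is assumed.
- 12 patients per group (section 4.3).
- Between-group tests: VAS and one SF-36 domain by Mann-Whitney (2), AMP and seven SF-36 domains by t-test (8). Total 10, of which 2 are primary. The questionnaire has no test.

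**Does the sample size identify the leading outcome?** No. Section 4.3 says "Sample size is 6 in each group calculated by openEpi (24). We included 12 patients in each group" and gives no outcome, effect size, SD or power. The figure of 6 cannot be reproduced, so it does not show which primary the trial was built on.

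**Family-wise error under independence**, 1 − 0.95^k:
- two primaries: 1 − 0.95² = 1 − 0.9025 = 9.75%
- eight SF-36 domains: 1 − 0.95⁸ = 1 − 0.6634 = 33.7%
- all ten: 1 − 0.95¹⁰ = 1 − 0.5987 = 40.1%

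**Allowing for correlation.** The documents give no correlations, so a range is assumed. Null trials were simulated (8,000 runs, normal data, 12 per group, the named tests, equal correlation between outcomes, one visit). Entries are the chance of at least one p<0.05:

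| Assumed correlation | VAS and AMP | All ten tests |
|---|---|---|
| 0 | 9.5% | 39.3% |
| 0.3 | 10.0% | 34.4% |
| 0.5 | 8.7% | 28.6% |
| 0.7 | 7.7% | 21.9% |

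The Monte Carlo standard error in the first column is about √(0.095 × 0.905 / 8000) = 0.3 percentage points, so its first two rows are not distinguishable. In round terms the error is 8-10% for the primaries and 22-40% for all ten tests.

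**What an adjustment would require**
- Holm over VAS and AMP compares the smaller p-value with 0.05/2 = 0.025. AMP is reported as not significant, so VAS has the smaller p-value and must meet 0.025.
- Holm over eight domains starts at 0.05/8 = 0.00625. The other seven are reported as not significant, so bodily pain must meet 0.00625.
- Both are reported only as p<0.05, so neither can be checked from the documents.

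**The case against.** The case on the other side has real weight.

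- **SF-36 is labelled secondary.** This stands. Pooling its domains with the primaries into one family of ten is an analyst's choice, and 22-40% is not the error rate of a primary claim. The figure for that is 8-10%.
- **The summary is open about the null results and claims only better pain management.** This also stands. What is missing is a plain statement that the broader hypothesis was not met.
- **The MANOVA could protect the later tests.** It could if it were a gate, but the text gives it a different role and makes no later test depend on it.
- **Requiring benefit on every outcome would not inflate error.** True: in the simulation, all ten tests were significant together in 0.1% of null trials or fewer. But the text states an expectation, not a decision rule, and the conclusion does not follow it.

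A reader might infer four stronger points that the documents do not support.

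1. *A false positive is likely.* At week 4 the chance stays at about 40% or below, and at about 10% or below for the primaries.
2. *Both visits are tested.* If they were, the simulated error over ten outcomes would be 36-60% (outcome correlation 0.7 to 0, assumed correlation 0.6 between visits), or 64% with all 20 tests independent. Collection at week 2 is stated, but testing is not, and the outcome time frame is 4 weeks.
3. *Three primaries are tested, giving 14.3%.* The questionnaire has no test and adds no error; it is a labelling fault.
4. *The trial is negative by its own rule.* Success cannot be both undefined and failed. The hypothesis was not met, but no rule makes that the verdict on the trial.

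**Conclusion.** The point holds and should be fixed. The primary list contains a measure that is not an outcome, the two testable primaries have no ranking or success rule, and ten between-group tests share one unadjusted 0.05. The sizes given above rest on assumed correlations, two-sided tests, one tested visit and, for the primaries, a win on either one counting as success.

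The effect on the conclusion is limited but real. The pain claim may well survive, but the documents do not let a reader confirm it, and the bodily-pain finding is weaker support than its place beside VAS suggests. Disclosure of the null results and the modest inflation for the primaries keep this below a must-fix.

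**What to change.** - Move the questionnaire from section 4.6 to screening.
- State that the between-group tests are at week 4 and that week 2 is supportive.
- Keep VAS and AMP as the two primaries and apply Holm across them. Section 1 already reports results, so making VAS the sole primary, demoting AMP, or replacing the domains with PCS and MCS would now be choices driven by the data.
- Apply Holm separately across the eight SF-36 domains, or label them exploratory.
- Say that the adjustment was chosen after results were known, and report exact and adjusted p-values for all ten tests.
- State in the conclusion that the hypothesis of improvement on every outcome was not met and that any benefit is limited to pain.

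**Cost.** No new data are needed, only reporting of existing p-values and revised wording. The VAS claim is lost if its p-value lies between 0.025 and 0.05, and the bodily-pain claim is lost if its p-value exceeds 0.00625. For scale, with 12 per group the standardised difference detectable at 80% power by a two-sided t-test rises from 1.20 at 0.05 to 1.34 at 0.025. Two separate Holm families hold 5% each, so the bound over both together is 0.05 + 0.05 = 10%; this is acceptable if SF-36 is read as secondary.

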**8. Quality assurance**

Yes, it was followed

**9. Expected outcomes of the study**

It was hypothesized that addition of phantom exercises would result in significantly improved clinical outcome in all studied parameters. Because of high prevalence and high pain intensity of phantom limb pain, there is need to find an effective, easily administered home based treatment for amputees, thus comparing effects of mirror therapy with and without phantom exercises in reducing pain and improving QOL and psychological status of amputees is a useful guide for future studies as these protocols are cost effective and efficient.

**10. Dissemination of results and publication policy**

It will be presented in conference, faculty meeting, professional gathering, publication. Etc

**11. Duration of the project**

Duration of project was 12 months after the approval of synopsis. (February 26, 2020 to March 30, 2021)

**12. Problems anticipated**

There may be lack of follow up or literacy ratio can affect outcome of study. Urdu based brochure helped natives to understand exercises and these problems were not faced during data collections.

**13. Project management**

AZ and SF were responsible for data control, monitoring intervention in order to detect any adverse effects, data analysis and manuscript writing. TM performed formal analysis, and validation of study data. [name] was responsible for the development of study design and project coordination as well as he reviewed and revised manuscript. All the authors further approved the final version of manuscript.

**15. Ethics**

Ethical approval was received from Ethical Review Committee of Riphah College of Rehabilitation and Allied Health Sciences, Riphah International University, Lahore (Reference number: REC/RCRS/20/2008). All ethical rules and regulations were followed while conducting the study and the participants were included in the study on the basis of informed consent.

**Research protocol: part 2**

**1. Budget**

No budget as such, research bears expenses, no financial support

**2. Other support for the project**

None.

**3. Curriculum Vitae of investigators**

Please find uploaded CV.

**4. Financing and insurance**

No funding sources.
